#### Postoperative morbidity

The following set of predefined complications will be considered as adverse events and documented:Anastomotic leakage: Communication between the intraluminal and extraluminal compartments due to a defect of the integrity of the intestinal wall at the site of the anastomosis. Clinical findings suspicious of leakage (i.e., abdominal pain, fever, elevated infectious parameters, or feculent drain content) must be confirmed by contrast-enhanced CT or during relaparoscopy or laparotomy.Postoperative hemorrhage: Any drop of hemoglobin > 3 g/dl (6 h after the end of surgery), any postoperative transfusion of packed red blood cells for a falling hemoglobin value, or hemorrhage requiring re-intervention (i.e., embolization or laparotomy).Intraabdominal fluid collection/abscess: Intraabdominal fluid collection detected on any imaging modality (e.g., ultrasound or CT scan) associated with abdominal discomfort/pain or elevation of infectious parameters.Wound infection: Pain, redness, and swelling of the wound that requires opening of the wound or antibiotic therapy.Pneumonia: Pulmonary infection with evidence of increased infection parameters (CRP > 20 mg/l and/or white blood cell count > 10 × 10^9^/l) that are unlikely to be caused by a different pathologic process and evidence of pulmonary infiltrates on chest X-ray, which require antibiotic therapy.Mortality: Death due to any cause during the patient’s initial hospital stay and within 30 days after surgery (by calling the patient by phone).Need for invasive re-intervention: Need for re-laparoscopy, laparotomy, or other interventions (e.g., drainage) during the patient’s initial hospital stay.

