**Methods/design:**

Patients scheduled for elective laparoscopic colectomy or upper rectum resection are eligible to participate in this double-blinded, placebo-controlled, randomized trial. Patients fulfilling all inclusion criteria will be allocated after the surgical procedure to one of three treatment arms: 100 mg caffeine, 200 mg caffeine, or placebo (corn starch). Patients will take the capsules containing the study medication three times daily with a meal. The primary endpoint of the study is the time to a solid bowel movement. The study treatment will be stopped after the patient produces a solid bowel movement or has taken ten capsules, whichever occurs first. To determine the colonic passage time, patients will take a capsule with radiopaque markers at breakfast for the first 3 days after surgery. On the fourth day, the location of the markers will be determined with an abdominal X-ray scan. Further secondary objectives are the postoperative morbidity and mortality, well-being, sleeping behavior, and length of hospital stay.

The study size was calculated to be 180 patients with an interim analysis occurring after 60 patients.

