**Discussion:**

From a previous study investigating coffee, evidence exists that caffeine might have a positive influence on the postoperative bowel activity. This double-blinded, placebo-controlled, randomized trial tries to show that caffeine will shorten the postoperative bowel paralysis and, thus, will improve recovery and shorten the hospital stay after colon surgery.

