### Outcomes

The primary outcome of the study will be the return to normal bowel function after colon resection. The primary endpoint will be the time to the first bowel movement after surgery. Secondary objectives are the safety of the caffeine treatment, particularly the degree and perception of the known effects of caffeine, such as agitation and insomnia, and the recovery from surgery, morbidity, and mortality.

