### Data collection and monitoring

Patients will be hospitalized during the whole study (due to the colectomy). Thus, study participants are under steady monitoring by surgeons and regular nursing staff. Furthermore, a dedicated study nurse will collect data from the patients’ records and will ask the patients directly for the key endpoints (time to first flatus, time to bowel movement, etc.). This study nurse will also deliver and collect the questionnaires from the patients and will help them with the questionnaires if the patient so wishes.

Data will be collected with a custom-made software with extensive data-entry checks (numerical data are restricted to plausible ranges, and categorical data entry is performed via pull-down menus or option buttons). Entry forms for questionnaires have the same layout as the questionnaires themselves. Thus, correct data entry can be confirmed by simple pattern comparison. Data entry is recorded in an audit log, the data set can be restored to the state of the last five close events, and an overnight backup to a remote server is performed daily.

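### Invasive re-intervention is counted only until first discharge, so it would be under-counted with caffeine if caffeine shortens the stay, although a 30-day call is already planned

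*Protocol article*

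**What the plan says.** Under Postoperative morbidity the protocol article introduces a list of seven items: "The following set of predefined complications will be considered as adverse events and documented". The last two carry different observation windows.

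- Mortality covers death from any cause during the "initial hospital stay and within 30 days after surgery (by calling the patient by phone".
- Need for invasive re-intervention covers re-laparoscopy, laparotomy or "other interventions (e.g., drainage) during the patient’s initial hospital stay".

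The other five items (anastomotic leakage, hemorrhage, fluid collection or abscess, wound infection, pneumonia) have no stated window.

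Three other places bear on this:

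- Outcomes names "the recovery from surgery, morbidity, and mortality" among the secondary objectives.
- Endpoints lists passage of stool among the criteria for discharge, together with freedom from other complications. It adds that insurance and social reasons can prolong the actual stay.
- The Discussion part of the abstract says the trial tries to show that caffeine "will improve recovery and shorten the hospital stay after colon surgery". Length of stay is itself a secondary objective in the abstract.

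**The concern.** The window for re-intervention closes at discharge, and discharge lies on the pathway that caffeine is meant to act on: earlier stool removes one barrier to going home. If the hypothesis is true, caffeine patients are observed for less time on this item. Equal true risk would then give fewer recorded re-interventions with caffeine, an apparent benefit produced by the definition.

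There is also a loss that does not depend on any difference in stay. A patient who goes home and is readmitted for drainage or reoperation counts as having had no re-intervention. A trial that hopes to bring discharge forward needs to know how often that happens.

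**Working it through.** **The plan's own figures.** The article gives no figure for re-interventions. Its sample size (Sample size calculation) reproduces. With a 10 h difference, SD 20 h, 80% power, two-sided alpha 0.05 and allocation 1:2, the placebo group needs (1.960 + 0.842)² × 20² × (1 + 1/2) / 10² = 47.1, so 48. That gives 48 + 96 = 144, and 144 / (1 − 0.20) = 180. The present point does not depend on these numbers. It takes from that section only the 10 h, the one planned effect in the article, which refers to bowel movement and not to discharge.

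**Check 1: constant daily rate (assumption).** Recorded events are proportional to days observed. If the stay falls from L to L − d at equal true risk, the share lost is d / L. The stays of 5 and 7 days are assumptions.

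| Placebo stay L | Shortening d | d / L | Fewer events recorded |
|---|---|---|---|
| 7 days (168 h) | 10 h | 10/168 | 6% |
| 5 days (120 h) | 10 h | 10/120 | 8% |
| 7 days (168 h) | 24 h | 24/168 | 14% |

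**Check 2: other time patterns.** Let p be the 30-day risk, equal in all arms, and F the distribution of time to re-intervention. The recorded risk is p × F(stay) / F(30), and the spurious risk ratio is F(L − d) / F(L), whose true value is 1.00. Assumptions, none from the article: p of 5% or 10%; median time to re-intervention 5 or 8 days, exponential or lognormal (log-scale SD 0.6); placebo stay 5 or 7 days.

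One case in full, exponential with median 5 days, L = 7 days, d = 10 h (0.417 days), p = 5%:

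- F(7) = 1 − exp(−0.1386 × 7) = 0.621 and F(30) = 0.984, so the recorded placebo risk is 0.05 × 0.621 / 0.984 = 3.15%.
- F(6.583) = 0.598, so the recorded caffeine risk is 3.04%.
- The ratio is 0.964.

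Across all cases:

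- Stay shorter by 10 h: risk ratio 0.82 to 0.96.
- Stay shorter by one day: risk ratio 0.57 to 0.91.
- Absolute differences: about 0.1 to 1.5 percentage points.
- Share of placebo-arm 30-day re-interventions occurring after discharge and so missed: about 29% (1 − 3.57/5.00) to 78% (1 − 1.10/5.00).

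**In events.** With 60 placebo and 120 caffeine patients, p = 5% means 3 and 6 re-interventions by day 30, and p = 10% means 6 and 12. In the worked case the unbiased in-stay count for caffeine would be 2 × 1.89 = 3.78, against 3.65 recorded, a shortfall of 0.13 events. The largest shortfall in the grid (p = 10%, lognormal, median 5 days, 5-day stay, one day shorter) is 2 × 3.00 − 4.27 = 1.73 events.

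**With a fixed 30-day window.** The recorded risk is p in every arm, and the ratio is 1.00 whatever the difference in stay.

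**The case against.** The strongest case against the point is that the effect is conditional and small. It needs caffeine to shorten the actual stay, and the article's own Discussion calls the hypothesis speculative. Insurance and social reasons weaken the link from bowel movement to discharge. Discharge also requires freedom from complications, so a patient already developing one tends to stay in hospital and inside the window; both checks ignore this and so tend to overstate the bias. They also carry the whole 10 h through to discharge. With few events expected, random error will exceed the bias. All of this stands and limits the size. It does not remove the stay-dependent rule, and it does not touch events that first appear after discharge.

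It can also be said that some re-interventions surface under other items: hemorrhage includes bleeding that needs re-intervention, and leakage may be confirmed at reoperation. That is partly true, but it does not restore the re-intervention count itself.

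A reader might infer more: that the whole safety comparison is biased, because "Patients will be hospitalized during the whole study (due to the colectomy" suggests that every complication is collected only in hospital. The article does not support this. That sentence is a general remark on monitoring, and it cannot be a literal limit because mortality is followed "within 30 days after surgery (by calling the patient by phone". Five of the seven items have no stated window, and a condensed article may leave that to the full protocol. Mortality has its own 30-day window, and the caffeine side-effect questionnaires are given on fixed days 2 and 4.

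**Conclusion.** The point holds for the re-intervention item. The article states a window for it that ends at an event the treatment is meant to bring forward, while the neighbouring item has a fixed one. If caffeine shortens the stay, re-interventions would be under-counted in the caffeine arms at equal true risk. If it does not, there is no differential bias, but re-interventions after discharge are still missed in every arm.

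The size is probably modest: about 6% to 8% fewer recorded events for a stay shorter by 10 h and about 14% for one day off seven, under the assumed constant daily rate. Other assumed time patterns widen this to ratios of 0.82 to 0.96 and 0.57 to 0.91. Larger reductions in stay would give larger figures, but nothing in the article plans for them. The primary endpoint, its alpha and the sample size are unaffected. The change is worth making because the rule is easily replaced and the missing events are the ones that matter when discharge comes earlier.

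**What to change.** Define need for invasive re-intervention from surgery to day 30 in all three arms. Ask about re-intervention and related readmission in the 30-day call already planned for mortality, and confirm the answers from hospital records where possible. Keep the in-hospital count as a descriptive result. The same window can be stated for the other listed complications for consistency.

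The cost is a few questions in an existing call and a few lines on the data form; the 180 patients stay as planned. The downside is that post-discharge events are partly patient-reported. The Trial status section reports 12 patients randomized by 7 March 2016, so a change made at that point would cover nearly the whole trial.

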#### Caffeine, nicotine, and sleeping habits evaluation

Before surgery, patients will be asked about their caffeine and nicotine consumption and their sleeping behavior as a reference for the following endpoints.

#### Well-being

No classical quality-of-life instruments (such as the SF36 or EORTC QLQ-C30) will be administered because these usually cover periods of 14–28 days, which would be too long for this study. In addition, no reason exists to assume that the quality of life would differ between the treatment and placebo group, statistically or clinically. Furthermore, a reference value would be difficult to find, as the quality of life is certainly impaired before surgery. Thus, well-being with respect to the mental state will be measured for this study, which describes the current mood and state of the patient. The Basel Mental State Scale (Basler Befindlichkeits-Skala BBS), which consists of 16 bipolar items (a choice between two properties, such as tired/awake) will be used for this study. The instrument, which covers four domains (vitality, balance, extraversion, and vigilance), is well established, validated, and suitable for Swiss and German populations (the scale was developed in Switzerland) [13]. Patients will be asked to fill in the form on the afternoon of the second and fourth day after surgery (during treatment versus after treatment).

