#### Caffeine-related side effects

Patients will receive a self-administered questionnaire concerning the potential side effects of caffeine together with the well-being questionnaire mentioned above (i.e., on days 2 and 4). No established or validated instrument could be found for this purpose. Thus, the questionnaire was adopted from Liguori et al. [14] and complemented with questions regarding sleep and the patient’s self-assessment on whether the patient actually received caffeine. In addition, the established and validated Leeds sleep-evaluation questionnaire will be administered [15–17].

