**Fig. 1 Fig1:**
[figure not shown]
Time course of the study treatment. Study treatment starts the evening of surgery if wound dressing was applied before 1 p.m.; otherwise, in the morning of the next day. Study treatment continues until the first solid bowel movement or until ten capsules have been taken (whichever occurs first). The *dotted line* at both ends of the study treatment period indicates that the start and end of the study treatment can vary according to the above-stated rules

If the wound dressing was placed before 1 p.m., the first capsule will be given in the evening; otherwise, in the morning of the following day. Patients will take a total of ten capsules, one with each meal (three times daily). However, the medication will be stopped after the primary endpoint (normal bowel movement) has been reached. The remaining capsules will be returned to the study center. A placard will be attached to the patient bed to indicate study participation and that the patient is not allowed to consume caffeine-containing beverages or food.

In addition to the study treatment, the patients will take a capsule with radiopaque markers every morning starting with the day after surgery for 3 days. On day 4 after surgery, a patient will undergo X-ray imaging to determine the location of the markers to determine the colonic passage time.

Otherwise, the treatment will not differ from the treatment of the colectomy received outside of the study, including the treatment of an ileus after the end of the study period. In case of an ileus after the patient has taken the last study medication, the underlying medical conditions will be corrected, in particular, electrolyte or acid-base abnormalities. Patients suffering from vomiting or distention will receive a nasogastric tube. Finally, patients with an ileus will receive laxatives (magnesium salts, Laxoberon, and one enema/day) and prokinetic drugs (erythromycin 3 × 100 mg/day i.v. for 3 days, and 12–24 h later, metoclopramide 10–30 mg/day iv, together with neostigmine 0.5–1.5 mg iv).

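### The day-2 forms are not reliably on-treatment: capsules stop at the bowel movement, so exposure at that form depends on the primary outcome and, if caffeine works, differs by arm

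*Protocol article*

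**What the plan says.** The Outcomes section makes safety a secondary objective, "particularly the degree and perception of the known effects of caffeine, such as agitation and insomnia". Two sections of the protocol article set the timing of the patient-reported forms. Under Well-being, the Basel scale is completed "on the afternoon of the second and fourth day after surgery (during treatment versus after treatment". Under Caffeine-related side effects, the side-effect questionnaire is handed out "together with the well-being questionnaire mentioned above (i.e., on days 2 and 4". The same section adds the sleep form, "In addition, the established and validated Leeds sleep-evaluation questionnaire will be administered", without giving it a day or a recall period.

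The Study outline sets the treatment period. If the "wound dressing was placed before 1 p.m., the first capsule will be given in the evening; otherwise, in the morning" of the next day. The maximum is fixed as follows: "Patients will take a total of ten capsules, one with each meal (three times daily". The stopping rule is: "However, the medication will be stopped after the primary endpoint (normal bowel movement) has been reached".

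The stopping event is worded in more than one way. The Abstract and the Fig. 1 legend refer to a solid bowel movement. The Study outline text refers to a normal one and equates it with the primary endpoint. Outcomes and Endpoints define that endpoint as the first bowel movement.

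**The concern.** The forms are tied to calendar days, while the treatment period is tied to the patient's bowel function. A patient whose bowels move before the afternoon of day 2 has stopped capsules, yet fills in a form that the plan regards as completed during treatment. These are the early responders, and if caffeine does what the trial hopes, there are more of them on caffeine.

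Two consequences follow. First, the day-2 comparison between arms mixes exposed and no longer exposed caffeine patients, so a transient effect such as restlessness is diluted. The better caffeine works, the stronger the dilution and the safer caffeine looks. Second, restricting the comparison to patients still taking capsules does not repair this, because that subset is selected by the primary outcome. The Well-being section says the scale describes current mood and state, so exposure at the time of completion matters.

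**Working it through.** **The plan's own figure.** No figure is stated for the forms. The sample size is used below, so it was checked first: placebo n = (1.960 + 0.842)² × (1 + 1/2) / 0.5² = 47.1, rounded up to 48. With 96 on caffeine the total is 144, and 144 / 0.8 = 180. Both stated totals reproduce.

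**Capsule calendar from the Study outline.**
- Evening start: 1 + 3 + 3 + 3 = 10, the last at the evening meal of day 3.
- Next-morning start: 3 + 3 + 3 + 1 = 10, the last at breakfast on day 4.

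On schedule, every capsule precedes the day-4 afternoon form.

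**Inputs.** From Sample size calculation (open surgery, with coffee standing in for caffeine): 61.5 ± 18.5 h on coffee, 72.5 ± 19.5 h on placebo. Assumed: normal times, breakfast 08:00, evening meal 18:00, form at 15:00, wound closure at 11:00 (evening start) or 16:00 (morning start). The Background says open surgery takes longer but gives no amount; a 10 h shift is assumed to show the range.

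**Share stopped by the day-2 form** = Φ((t − mean)/SD), where t is 52 h (closure 11:00) or 47 h (closure 16:00).

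| | t | Caffeine | Placebo |
|---|---|---|---|
| No shift | 52 h | Φ(−9.5/18.5) = 30% | Φ(−20.5/19.5) = 15% |
| No shift | 47 h | Φ(−14.5/18.5) = 22% | Φ(−25.5/19.5) = 10% |
| 10 h shorter | 52 h | Φ(0.5/18.5) = 51% | Φ(−10.5/19.5) = 30% |
| 10 h shorter | 47 h | Φ(−4.5/18.5) = 40% | Φ(−15.5/19.5) = 21% |

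The earlier study's published values (60 ± 21 h and 74 ± 21 h, same section) give a similar picture without shift: Φ(−8/21) = 35% and Φ(−13/21) = 27% on caffeine, against Φ(−22/21) = 15% and Φ(−27/21) = 10% on placebo.

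**Stricter count: no capsule at all on day 2** (bowel movement before breakfast, t = 45 h or 40 h). Caffeine: Φ(−16.5/18.5) = 19% or Φ(−21.5/18.5) = 12%. Placebo: Φ(−27.5/19.5) = 8% or Φ(−32.5/19.5) = 5%. With the 10 h shift, caffeine is 36% or 27%.

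**Day 4.** Evening starters take no capsule that day. For a morning starter (closure 16:00, breakfast at 88 h), the share still due the tenth capsule is 1 − Φ(26.5/18.5) = 8% on caffeine and 1 − Φ(15.5/19.5) = 21% on placebo. With the shift this is about 2% and 10%.

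**Evening capsule on day 3** (79 h or 74 h), relevant only if the sleep items cover the previous night. Caffeine: 1 − Φ(17.5/18.5) = 17% or 1 − Φ(12.5/18.5) = 25%. Placebo: 37% or 47%. With the shift, caffeine falls to 7% or 11%, and placebo to 20% or 28%.

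**Dilution, for illustration.** If patients who have stopped show no residual effect, an effect d becomes d × (1 − share of caffeine patients stopped). Take d = 0.5 SD, 48 against 96, and SE = √(1/48 + 1/96) = 0.177.

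| Share stopped | Effect | Power, Φ(effect/SE − 1.96) |
|---|---|---|
| 0% | 0.50 | 81% |
| 30% | 0.35 | 51% |
| 50% | 0.25 | 29% |

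**The case against.** **Fixed days are a sound design.** They compare randomised arms at equal recovery time under the regimen as used. This stands, and it is why the forms should not be moved to the day of the bowel movement: assessment time would then depend on the outcome, and more caffeine patients would be assessed nearer surgery. It does not rescue the on-treatment label.

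**Stopping before the form is not the same as being unexposed.** A patient whose bowels move between breakfast and 15:00 had a capsule that morning, and the side-effect form states no recall window. This also stands. The stricter count of 12–19% on caffeine is the more cautious figure, and the dilution table is an upper illustration.

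**The stopping event may be later than the first stool.** If treatment ends only at a solid movement, fewer patients have stopped by day 2. The documents do not settle this. The share would fall, but its dependence on bowel recovery would remain.

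**Exposure can be derived, and other safety data exist.** Bowel-movement time is recorded and unused capsules are returned. Pulse and blood pressure are usually recorded three times daily, and sleep-inducing drugs and adverse events are also captured. So the dilution concerns these forms and not the whole safety objective. However, the listed postoperative complications do not include agitation or insomnia, and the patient's own perception of them rests largely on the forms.

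**A reader might infer that many day-4 forms are completed on drug.** The documents do not support that. All ten capsules precede that afternoon, and only a few late starters on caffeine take one that morning. Nor can the day-2 and day-4 problems both be large: faster recovery after laparoscopy raises the first and shrinks the second. The sleep version of the day-4 point needs a previous-night recall window that the article does not state.

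**Conclusion.** The point holds for day 2. The on-treatment label there conflicts with the stopping rule, and exposure at that form is decided by the primary outcome. On the open-surgery values about 22–30% of caffeine and 10–15% of placebo patients have stopped; about 12–19% and 5–8% have had no capsule that day. With an assumed 10 h shorter time, 40–51% and 21–30% have stopped. These shares rest on normality, the assumed clock times, the coffee data as a stand-in for caffeine, and the first bowel movement as the stopping event. A day-2 comparison read as on-treatment tolerability would understate transient caffeine effects, by an amount that depends on residual effect and recall window.

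The day-4 label fits the schedule, apart from a last breakfast capsule in a few late starters and, if the sleep items look back one night, a day-3 evening capsule in a minority of caffeine patients. The primary analysis is unaffected. The change is worth making because it corrects what the trial can conclude on tolerability at almost no cost.

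**What to change.** 1. Keep the forms on days 2 and 4 for all patients.
2. Record on each form the number of capsules taken so far and the time of the last one.
3. Report exposure at each form by arm.
4. Analyse the forms by randomised arm, as the effect of the regimen as given. Remove the during-versus-after label and do not interpret the two days as that contrast.
5. Present any analysis by exposure as descriptive, because exposure is selected by outcome.
6. Reconcile the passages that describe the stopping event as solid (Abstract, Fig. 1 legend), normal (Study outline) and first (Outcomes, Endpoints), since the share off drug depends on them.

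Treatment is unchanged. The cost is one extra entry per form, made by a study nurse who already asks patients daily, and a weaker claim about on-treatment tolerability. With 12 patients randomised as of 7 March 2016 (Trial status), nearly all the data would benefit.
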